## Assignment of interventions: blinding

### Who will be blinded {17a}

Trial participants and the team members performing assessments are double-blinded.

### Procedure for unblinding if needed {17b}

The team members performing data analysis are not blinded. There will be no need for unblinding participants and the team members performing assessments, who will not be involved in the data analysis and will not be informed of the order of treatment.

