**Fig. 1 Fig1:**
[figure not shown]
Neural mechanism and the experimental design in this study. **a** The two main motor areas involved in stroke recovery: the primary motor cortex and the dorsal premotor area. **b** Motor descending pathways in stroke recovery. **c** The first intervention involves stimulating the iM1 area using anodal stimulation. **d** The second intervention involves stimulating the cPMd using cathodal stimulation. **e** The third intervention combines anodal stimulation of the iM1 area and cathodal stimulation of the cPMd. **f** The sham condition without any stimulation intervention

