### Outcomes {12}

#### Primary outcome measure

In this study, the primary outcome measure is transcranial magnetic stimulation (TMS) induced motor evoked potentials (MEP) latency and status [14, 15]. These allow the research team to determine the location of the ipsilesional corticospinal tract and the contralesional cortico-reticulospinal tract [14, 16]. Electromyography (EMG) electrodes are applied to the biceps brachii, triceps brachii, brachialis, and deltoid muscles to record muscle response to TMS. Researchers apply the paired-pulse TMS (Magstim® BiStim2, The Magstim Company Ltd., Spring Gardens, Whitland, UK) to the approximate location of the corticospinal tract origin in ipsilesional motor cortex associated with the biceps brachii and the brachialis muscles in the paretic arm. Researchers also apply the TMS to the approximate location of the origin of the cortico-reticulospinal tract utilizing a figure-eight coil [14]. Researchers utilize a paired-pulse TMS with a conditioning pulse at 65% stimulator maximum intensity and follow with a testing pulse at 85% stimulator maximum intensity. This procedure avoids any need to pre-activate the muscle which could cause bias of background EMG [16]. Researchers use paired pulse intervals of 25 ms [14]. Researchers place the center of the coil tangentially to the skull with the handle at 45° from the parasagittal plane: posterior-anterior orientation for ipsilesional M1 and anterior–posterior orientation for contralesional PMd (Fig. 1a) [17, 18]. Researchers define the M1 stimulation location as being on the grid point that results in the largest response in the target muscle. This target is found for the ipsilesional M1 and contralesional M1 hemisphere through stimulation of a 5 × 5 grid of 1 cm spaced sites on the scalp over motor areas of each hemisphere (centered at C3/4 of 10–20 EEG system) [15]. The target of the contralesional PMd is identified using a reference point of 1 cm medial and 2.5 cm anterior of the M1 target at the contralesional hemisphere [17, 19]. Previous research suggests [20] the participant is considered MEP + if MEPs of any amplitude are observed at a consistent latency on at least 5 out 10 trials. If not, the participant is considered MEP − . At least eight additional pulses with an inter-stimulus interval of 2–3 s are applied to the target to obtain an accurate estimate MEP latency. Researchers then calculate the average latency and amplitude of MEP within all positive trials.

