### Concealment mechanism {16b}

The blinded team members will leave the room when the intervention is performed. The participants are also blinded to the intervention. The interventions for sham, anodal, cathodal, and bilateral stimulation require the same process and length of time and are indistinguishable from the participant’s perspective.

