### Implementation {16c}

The randomization order is also generated by a random sequence generator provided by REDCap (Research Electronic Data Capture) [26, 27]. If participants express interest in participating in the study, a sub-investigator will contact them by phone and schedule an appointment. On this visit, research staff will explain the study to them and go through the consent process. After consent is obtained from the participant, the assessments and interventions are performed by trained research staff. The allocation sequence is generated by a member of the team who is not involved in subjective outcome measures including the Fugl-Meyer and MAS.

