### Adverse event reporting and harms {22}

Potential adverse effects of tDCS are listed in the consent form and include tingling or warm sensation at the beginning of stimulation, mild, brief headache, redness of the skin under the EMG or intervention electrodes, fatigue, dizziness, or nausea after participating in the experiment. All of these effects are expected to fade soon after the experiment is completed. If participants experience any adverse effects, they report them to the principal investigator, who determines how to proceed. All adverse events are reported to the institutional review board (IRB) as well as the funding agency. The PI holds bi-weekly meetings with team members to review all reportable new information.

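### Data analysts are left unblinded, and nothing in the article keeps scoring of the judgement-based primary MEP outcome, or finalisation of the analysis, masked to arm; the sham descriptions also need reconciling

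*Protocol article*

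**What the plan says.** All references are to the Protocol article.

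- **Who is blinded {17a}:** "Trial participants and the team members performing assessments are double-blinded".
- **Procedure for unblinding {17b}:** "The team members performing data analysis are not blinded". The same section describes the participants and assessors as people "who will not be involved in the data analysis and will not be informed of the order of treatment".
- **Primary outcome measure:** the outcome is MEP latency and status. A participant is MEP-positive "if MEPs of any amplitude are observed at a consistent latency on at least 5 out 10 trials". Latency and amplitude are then averaged over the positive trials. The work is attributed to researchers, with no role named.
- **Table 1 and Plans for assessment {18a}:** TMS is listed under assessments beside FM-UE and MAS. Assessments are done by an investigator who takes no part in intervention or randomization.
- **Implementation {16c}:** the allocation sequence comes from a team member "who is not involved in subjective outcome measures including the Fugl-Meyer and MAS".
- **Sham:** the Fig. 1f caption reads "The sham condition without any stimulation intervention". Explanation for the choice of comparators {6b} calls sham a mock session meant to keep patients blinded. Concealment mechanism {16b} says the four conditions "require the same process and length of time and are indistinguishable from the" standpoint of the participant. Adverse event reporting {22} lists "tingling or warm sensation at the beginning of stimulation" among the potential effects. Trial design {8} gives every participant all four conditions.

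**The concern.** There are two separate issues.

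**Scoring and analysis.** Deciding whether a small EMG deflection is an MEP, whether its latency is consistent with the others, and where its onset lies are all readings of a trace. The article gives no amplitude threshold and no latency tolerance. The same decision feeds both parts of the primary outcome, because latency is averaged only over trials called positive. The people stated to be blinded are excluded from the analysis, and the people doing the analysis are stated not to be blinded. If any trace reading is done after the visit as part of data processing, the reader may know the arm and whether the recording was made before or after stimulation. Choices made while the analysis is being finalised are open to the same knowledge.

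**Sham.** A participant who is told to expect tingling at onset, and who then attends four sessions, can compare them. If one session delivered no current at all, as the caption says, that comparison could reveal it. FM-UE is performance-based, so expectation could affect effort. Sham is the control for all three active conditions.

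**Working it through.** The article states no figure on this point, so the check sets the sections side by side. One illustrative calculation follows.

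**Step 1: does leaving analysts unblinded contradict double-blinding?** {17a} defines it as participants plus those performing assessments. {17b} openly says analysts are outside it. There is no contradiction.

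**Step 2: is the primary outcome inside the blinded part?** Table 1 puts TMS under assessments, {17a} blinds assessors, {18a} makes the assessor independent of intervention and randomization, {16b} has blinded staff leave the room during stimulation, and {17b} says assessors are not told the order. Acquisition of the TMS recordings is therefore covered.

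**Step 3: is scoring of the recordings inside it too?** The article does not settle this. Some responses must be read live, because the M1 target is chosen by the size of the response. Classification of trials and averaging of latency are assigned only to researchers. {17b} bars assessors from the analysis, so if scoring counts as analysis it falls to unblinded staff; if it counts as assessment it falls to blinded staff. Both readings are open.

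**Step 4: can a judgement on one trial matter?** Under the rule, MEP status changes between 4 and 5 positive trials out of 10. Let p be the probability of a response on each trial. Assume independent trials; neither p nor independence is in the document. The chance that a ten-trial block falls where one reclassified trial can flip the status is

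P(4 or 5) = C(10,4) p^4 (1−p)^6 + C(10,5) p^5 (1−p)^5

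| Assumed p | P(4 or 5 of 10) |
|---|---|
| 0.2 | 0.115 |
| 0.3 | 0.303 |
| 0.4 | 0.451 |
| 0.45 | 0.472 |
| 0.5 | 0.451 |
| 0.6 | 0.312 |
| 0.7 | 0.140 |

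For example, at p = 0.5 the sum is (210 + 252)/1024 = 0.451. One judgement can matter for participants with intermediate response rates. The table does not show that anyone scores with the arm known, or in which direction they would err.

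**Step 5: do the sham statements fit together?** Read literally, a session without any stimulation, conditions that a participant cannot tell apart, a sensation listed at the start of stimulation, and exposure of each person to all four conditions sit badly together. The mock-session description in {6b} does not say whether any current is delivered, so it does not resolve the conflict.

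**The case against.** **The strongest case against.** The limit on blinding is disclosed. The protections for assessors are general and not confined to FM-UE and MAS. The sentence in {16c} about subjective measures concerns only who generates the sequence, and its list is not exhaustive. TMS is an assessment in Table 1, so it lies with blinded, independent staff. Scoring workflow and sham delivery are details that an article may leave to the full protocol. On sham, a caption is a short label for a figure that is not shown, and may mean only that no active intervention is given. The listed sensations are potential effects: the article does not say that every participant feels them on active visits, or that the mock session produces none.

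**What stands.** All of this limits the point, but does not remove it. The point does not rest on a missing detail: the article positively fixes that analysts are not blinded and that blinded staff stay out of the analysis. A less bias-prone rule is available at little cost. Likewise, the sham point rests on two positive statements that sit badly together.

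**Stronger readings that the document does not support.** A reader might infer that the double-blind claim fails on the article's own terms; {17a} and {17b} rule that out. A reader might infer that scoring bias is present in the primary outcome; who scores the traces is not stated. A reader might infer that participants are unmasked; {6b} and the word potential in {22} leave that unproven. A reader might also count how many one-directional status changes would make a simple paired test significant. The plan uses GEE with intervention and time point as factors and an FDR correction, so such a count would not measure the risk here.

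**Conclusion.** The point holds as an avoidable bias risk in the primary outcome, plus a set of sham descriptions to reconcile. As written, the article permits MEP traces to be scored, and the analysis to be finalised, with the arm known. It does not show that this happens.

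The size of any bias cannot be obtained from the document. The only gauge is the illustration above: for assumed per-trial response rates of 0.3 to 0.6, about 30% to 47% of ten-trial blocks would lie where one re-read trial can change MEP status. That rests on independent trials and on rates the document does not give.

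The sham issue bears mainly on FM-UE, a secondary outcome, through participant effort and not through the rater. No route from it to the MEP outcome is shown. The change is worth making before scoring and analysis are completed.

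**What to change.** **Scoring and analysis.** In {17b}, replace the sentence saying that analysts are unblinded with:

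*EMG files are relabelled with codes hiding participant, arm, visit and pre/post before MEP status and latency are scored; analysts work with masked arm codes until scoring and the analysis programs are locked.*

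In the section on the primary outcome, name the role that scores the traces. Files already recorded can be relabelled in the same way.

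**Sham.** Reconcile the Fig. 1f caption with {6b}, {16b} and {22}, so that one consistent statement says what the sham session is and why participants are expected not to tell it apart. Which description is right is for the investigators to state.

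**Optional.** Ask participant and assessor at the end of each visit to guess active or sham, and report the guesses by arm. The plan is not wrong without this.

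**Cost.** Data handling is slightly slower, and an existing team member who does no scoring must hold the codes. The relabelling and rewording change no study procedure; the optional guess adds one question per visit.

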## Data collection and management

### Plans for assessment and collection of outcomes {18a}

A trained clinical investigator who is not involved in the intervention or randomization procedure will perform the assessments. Assessments will be performed at baseline and before and after the intervention at each visit.

### Plans to promote participant retention and complete follow-up {18b}

All intervention protocols are performed in the lab. A member of the research team will contact participants to schedule appointments. Participants receive a phone call the day before their appointment to confirm the meeting. If participants are late to their appointment, they are contacted to see if they are still coming or wish to reschedule. So far, the study has had a high retention rate. Participants are typically enthusiastic about the study and eager to return. As part of our effort to promote continued interest in the study, we strive to create a welcoming environment for participants and ensure that they understand and are included in the process.

### Data management {19}

All participant information, outcome measure recordings, consent forms, and HIPAA forms are stored in the secure data management program, Research Electronic Data Capture (REDCap) [26, 27]. REDCap is a secure, web-based software platform designed to support data capture for research studies, providing (1) an intuitive interface for validated data capture, (2) audit trails for tracking data manipulation and export procedures, (3) automated export procedures for seamless data downloads to common statistical packages, and (4) procedures for data integration and interoperability with external sources.

### Confidentiality {27}

Any paper versions of outcome measures, consent forms, or HIPAA forms are stored in a locked office. The raw/unprocessed data are coded with a unique participant identifier and will be stored in REDCap. Carle Research Institute uses REDCap (Research Electronic Data Capture) software https://redcap.carle.org/REDCap/ for building and managing online surveys and databases. Study data may be stored and accessed via REDCap. REDCap access and maintenance is provided by the Carle Research Institute. REDCap is password-protected. Raw data on the computer cluster is accessible only to study investigators.

### Plans for collection, laboratory evaluation, and storage of biological specimens for genetic or molecular analysis in this trial/future use {33}

N/A. No biological specimens are collected in this study.

## Statistical methods

### Statistical methods for primary and secondary outcomes {20a}

All outcome measures are continuous and correlated in a pretest/posttest format, requiring analysis with longitudinal linear modeling for correlated data analysis. We utilize generalized estimating equations (GEE) in SAS 9.4. GEE analysis is beneficial as it offers an unbiased estimation of population-averaged regression coefficients despite possible misspecification of the correlation structure even when the data is not normally distributed. Intervention type (anodal, cathodal, bilateral, and sham) and the time point (before or after stimulation) are defined as fixed factors. The study participants are defined as random factors. Carry-over effects will be examined using an extension of Grizzle’s classic crossover design [28]. All analyses are conducted using SAS 9.4 (Carey, NC) with an alpha = 0.05.

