### Sample size {14}

Study personnel aim to enroll up to 30 participants (15 female) in the event of a potential attrition rate of 15%. Based on our preliminary data [24], we estimated that the targeted effect size for our study is 0.42 (SD: 0.13). The power analysis was performed by using GLMMPSE Sample Size Software (https://samplesizeshop.org/) [25]. Based on our preliminary data from a pilot trial (ClinicalTrials.gov Identifier: NCT05174949) [24] and the proposed basic statistical analysis on the primary and secondary outcomes (see the “Statistical methods” section), we determined the sample size of 26 will give 80% power at the 5% significance level for the targeted effect size. We will include a total of 30 stroke participants (15 female) for this clinical trial study to account for an attrition rate of 15% based on our previous experience in similar multiple-visit brain stimulation research.

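### The primary model is defined both as GEE and as a model with random participants; with 26 to 30 participants the choice of model and of variance correction decides whether the 5% level is kept

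*Protocol article*

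**What the plan says.** Statistical methods for primary and secondary outcomes {20a} treats every outcome as continuous and correlated before and after stimulation. It names the method, "We utilize generalized estimating equations (GEE) in SAS 9.4", and gives as the reason that "it offers an unbiased estimation of population-averaged regression coefficients despite possible misspecification of the correlation structure". The model terms follow: "Intervention type (anodal, cathodal, bilateral, and sham) and the time point (before or after stimulation) are defined as fixed factors". The next sentence reads "The study participants are defined as random factors". The level is then set: "All analyses are conducted using SAS 9.4 (Carey, NC) with an alpha = 0.05".

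The same section does not say which variance estimator, test statistic or reference distribution goes with the GEE.

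Sample size {14} ties the sample size to the analysis in the statistical methods section and reports that "we determined the sample size of 26 will give 80% power at the 5% significance level for the targeted effect size". Thirty participants are to be enrolled, allowing for 15% attrition. The section on non-adherence and missing data {20c} removes participants who withdraw from the analysis.

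**The concern.** GEE describes the population mean and handles the correlation within a participant through a working correlation and a cluster-robust (sandwich) variance. It has no random effects. A model with participant as a random factor is a mixed model, whose standard errors come from the assumed variance components. An analyst cannot follow both sentences.

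The stated reason for choosing GEE also needs a qualification. Coefficients stay consistent under a wrong working correlation, but tests and intervals are protected only through the sandwich variance, and that protection is asymptotic in the number of participants. With 26 to 30 clusters the uncorrected sandwich variance is too small on average, and normal or chi-square critical values are too low. At stake is whether tests declared at 0.05 run at 0.05, and whether confidence intervals have their stated coverage. The false discovery rate correction in section {20b} works on the p-values it is given and does not repair a standard error that is too small.

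**Working it through.** **Inputs from the protocol.** 26 evaluable participants, 30 enrolled, 15% attrition (Sample size {14}; 30 × 0.85 = 25.5). Four interventions and two time points, so the intervention-by-time test has 3 df (section {20a}). Alpha 0.05 (section {20a}); sidedness is not stated, so two-sided is assumed.

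**The plan's own figure.** The sample size of 26 could not be reproduced. The metric of the effect size, the within-participant correlation and the hypothesis tested are not given. As a reference only: read as a standardized paired difference, 0.42 has 54% power at 26 participants and needs 47 for 80% (paired t-test, two-sided). With 26 participants, 80% power needs a standardized paired difference of 0.57. Nothing below depends on this; only the number of participants is used.

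**One active-sham contrast, uncorrected sandwich, Wald z.** Take the pre-to-post change under active stimulation minus that under sham, one value per participant, balanced data and normal errors. The uncorrected sandwich variance is (n−1)/n times the usual unbiased one. The test therefore rejects when |t(n−1)| > 1.96 × √((n−1)/n).

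- n = 26: threshold 1.96 × √(25/26) = 1.922; P(|t(25)| > 1.922) = 6.6%.
- n = 30: threshold 1.96 × √(29/30) = 1.927; P(|t(29)| > 1.927) = 6.4%.

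**3-df intervention-by-time test, uncorrected sandwich, Wald chi-square.** The statistic is Hotelling's T² up to the factor n/(n−1), so the test rejects when F(3, n−3) > 7.815 × (n−3)/(3n).

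- n = 26: 7.815 × 23/78 = 2.304; P(F(3, 23) > 2.304) = 10.4%.
- n = 30: 7.815 × 27/90 = 2.345; P(F(3, 27) > 2.345) = 9.5%.

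**Interval width.** The correct half-width at n = 26 is t(25, 0.975) × √(26/25) = 2.060 × 1.020 = 2.100 uncorrected standard errors, against 1.96. The ratio is 1.07, so a contrast interval would have to be about 7% wider.

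**Simulation check.** GEE with exchangeable working correlation, intervention-by-time, with and without period effects, 4,000 trials per setting, null true. The correction is Mancl-DeRouen with a t or F reference.

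| n | Uncorrected, per contrast | Uncorrected, 3 df | Corrected, per contrast | Corrected, 3 df |
|---|---|---|---|---|
| 26 | 6.4–6.8% | 10.1–10.4% | 4.3–4.6% | 4.4–4.7% |
| 30 | 6.2–6.8% | 8.9–10.0% | 4.4–5.1% | 4.3–4.9% |

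**Other readings of the same section, n = 26.**

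- Generalized score test, no variance correction: with W the Wald statistic, compare W/(1+W/n) with chi-square. This gives 4.8% (1 df) and 3.9% (3 df).
- Mixed model with random participant, compound symmetry correct, z or chi-square reference (an approximation): about 5.4% and 5.8%.

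So the true size of the 3-df test runs from about 4% to about 10%, depending on how section {20a} is read.

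**The case against.** The strongest reply is that the protocol nowhere says the standard errors are uncorrected, nor that Wald tests are used. Such details are commonly left to an analysis plan, which is not shown here. This stands. A reader might infer that the trial will run at 6.6% or 10.4%; the document does not support that. The figures describe one admissible reading, and the score test and the mixed model come close to 5% or fall below it.

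A second reply is that the conflict matters little, because under an identity link both models target the same mean contrasts. This also stands for the estimates, but not for their standard errors and reference distributions.

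Three further inferences are tempting and should not be drawn:

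- **Different estimands for MEP status.** Marginal and participant-specific effects differ under a non-linear link, but section {20a} plans linear modelling of outcomes it calls continuous and names no such link.
- **Power software that does not fit the analysis.** The protocol says "The power analysis was performed by using GLMMPSE Sample Size Software" and relates the calculation to its statistical methods section. It does not show which model was entered, so a mismatch cannot be established from it.
- **A missing-data advantage of the mixed model.** Section {20c} drops participants who withdraw, so that gain would require changing {20c} as well.

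Nor does the protocol give the proportion of participants with recordable MEPs, so error rates for a smaller analysed group would rest on assumption alone.

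**Conclusion.** The contradiction is in the text and does not depend on any unseen document: section {20a} names GEE and a random-participant model for the same analysis. The section must be reduced to one model.

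The size of the problem is conditional. With uncorrected Wald z or chi-square tests, balanced data and normal errors, type I error is 6.6% per contrast and 10.4% for the 3-df test at 26 participants, and 6.4% and 9.5% at 30. Other readings of the section show little or no inflation. Point estimates of the mean contrasts are not affected. The correction should be made, since it costs almost nothing, but this is not evidence that the planned analysis will exceed its level.

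**What to change.** Name one model in section {20a}. Either is acceptable:

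1. **Keep GEE.** Replace the random-factor sentence with a statement that the participant is the cluster. Require a small-sample variance correction (for example Mancl-DeRouen or Kauermann-Carroll) with t and F reference distributions. This keeps the stated rationale of robustness to the correlation structure.
2. **Use a linear mixed model.** Specify random participant, and visit within participant since pre and post values are both modelled, with Kenward-Roger degrees of freedom. Remove the GEE sentences. This gives up the stated rationale for GEE, so it is a choice and not a requirement.

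In Sample size {14}, state that the calculation refers to the model chosen.

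The cost is wording in two sections and slightly wider intervals: about 7% for a contrast at 26 participants, compared with uncorrected GEE intervals.
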